# Evaluating a Web-Based Mental Health Service for Secondary School Students in Australia: Protocol for a Cluster Randomized Controlled Trial

**DOI:** 10.2196/12892

**Published:** 2019-05-17

**Keywords:** schools, adolescent, mental health, depression, anxiety, mental health services, internet

## Abstract

**Background:**

Mental health problems are prevalent among Australian secondary school youth; however, help-seeking is low. Schools offer an ideal setting to address these concerns. The Black Dog Institute has developed a Web-based mental health service for secondary schools that is modeled on the principles of stepped care. The Smooth Sailing service aims to improve help-seeking and reduce anxiety and depressive symptoms in secondary school students. The acceptability of this service has been demonstrated in a pilot study. A full trial is now warranted.

**Objective:**

This study protocol for a cluster randomized controlled trial (RCT) aims to evaluate the effectiveness of the Smooth Sailing Web-based service for improving help-seeking intentions and behavior, and reducing depressive and anxiety symptoms, alongside other mental health outcomes, when compared with a school-as-usual control condition in secondary school youth.

**Methods:**

This RCT aims to recruit 1600 students from 16 secondary schools in regional and urban locations throughout New South Wales, Australia. Schools are randomly assigned to the intervention or school-as-usual control condition at the school level. Approximately 100 students from 1 or multiple grades are recruited from each participating school. Participants complete measures at 3 timepoints: baseline, 6 weeks post, and 12 weeks post, with the primary outcome assessed at 12 weeks posttest. Participants assigned to the intervention condition register to the Web-based service at baseline and receive care in accordance with the service model. Participants in the control condition receive school-as-usual.

**Results:**

The first baseline assessment occurred on February 22, 2018, with the
12-week endpoint assessments completed on Friday, June 29, 2018. Control schools are currently receiving the service, due for completion by June 30, 2019. The trial results are expected to demonstrate improved help-seeking intentions and behavior among students assigned to the intervention condition, alongside improvements in symptoms of depression, anxiety, distress, and other mental health outcomes when compared with students assigned to the control condition.

**Conclusions:**

To our knowledge, this is the first time that a Web-based mental health service based on the principles of stepped care will have been integrated into, and evaluated in, the Australian school context. The findings of this trial will have implications for the suitability of this type of service model in Australian schools and for the delivery of school-based mental health services more broadly.

**Trial Registration:**

Australian New Zealand Clinical Trials Registry ACTRN12618001539224 https://anzctr.org.au/Trial/Registration/TrialReview.aspx?id=375821&isReview=true (Archived by WebCite at http://www.webcitation.org/77N3MDGS6)

**International Registered Report Identifier (IRRID):**

DERR1-10.2196/12892

## Introduction

### Background

Adolescence is a key developmental period for mental illness with 50% of all mental disorders emerging before the age of 18 years [1]. As most young people spend these years in secondary education, schools now play an increasing role in addressing the mental health needs of their students. Schools are ideal settings for recognizing the early behavioral and emotional signs of mental illness among students and for trusted adults to initiate help-seeking [2]. This is important as youth are reluctant to seek formal care [2,3], despite the negative impacts of poor mental health on social and educational functioning [4-7]. Schools have initiated a range of programs aimed at reducing mental illness and improving mental health literacy among students, as well as increasing their likelihood of seeking help [8-11]. However, many of these programs lack evidence or have not had substantial uptake because of implementation barriers [12]. A total of 2 major challenges remain: identifying the students who are experiencing mental health problems and delivering care to those who require it.

Currently, most schools utilize a wait-to-act model in which the staff refer students to school counselling services, learning support or well-being teams after observing concerning behaviors or from students’ self-disclosures [13]. A more proactive approach, one that incorporates mental health screening and automatic stratification and response based on symptom severity, may improve schools’ capacity to address students’ mental health needs. Web-based stepped care presents a viable option for providing this type of care. This is based on the premise that simple, cost-effective Web-based psychotherapy is offered to youth with mild-moderate symptoms, with more costly, intensive face-to-face interventions reserved for those with more severe and persistent symptoms [14]. Although complex, this approach can be efficient, as it provides tailored help as required and aims to prevent serious mental illness by detecting symptoms early [15,16]. This type of care is also equitable, providing all students with an opportunity to have their mental health needs addressed. Internet screening and Web-based cognitive behavioral therapy (CBT) programs can be readily integrated into such a model as these require minimal human input, are acceptable to youth, preserve fidelity of care, and allow for ongoing monitoring and automated feedback [17]. Notably, this type of care system is engineered to reach out to youth rather than wait for them to approach.

Codesigned with students, school counsellors [18], general practitioners [19], and parents [20], the Black Dog Institute has developed a Web-based mental health service called Smooth Sailing. On the basis of the principles of stepped care, Smooth Sailing uses a website to screen, assess, allocate, and deliver psychological interventions to improve help-seeking for mental health problems and reduce depressive and anxiety symptoms among secondary school youth. This service uses brief, validated self-report measures for anxiety and depression [21,22] to accurately determine young people’s symptom severity and their required level of care. The service has 3 degrees of treatment intensity that are consistent with Australian Clinical Practice Guidelines [23]: self-directed Web-based psychoeducation for students with nil to mild symptoms, self-directed Web-based CBT for students with moderate symptoms [9,10], and a direct link to face-to-face care with a school counsellor for students with moderately severe to severe symptoms. Students are monitored fortnightly using a brief survey delivered via short message service (SMS) text messaging or email. Every 6 weeks, students complete a step assessment from which care is reallocated based on their results. If a student reports having thoughts of self-harm or death during any of the assessments, the school counsellor receives an automatic notification.

The Smooth Sailing service is designed as a universal intervention to improve young people’s attitudes toward seeking help for mental health problems. School-based screening has increased referral rates to health care services, demonstrating the positive impact that schools can have on initiating access to care [24,25]. Establishing healthy attitudes to help-seeking for mental health in adolescence, particularly from adults and professionals, is key to supporting lifelong mental health. A number of studies have revealed an association between positive attitudes to professional help-seeking and increased help-seeking intentions and behaviors in adolescents [26,27], university students [28], and adults [29]. The Smooth Sailing service is based on Rickwood et al’s [30] model in which help-seeking is defined as a process with 4 key stages. Outlined in Figure 1, Smooth Sailing attempts to target each of these stages through a range of different functions and content.

A 6-week single-arm pilot study of the Smooth Sailing service was undertaken in 4 New South Wales (NSW) secondary schools in 2017 with 59 students taking part. At posttest, 93% (55/59) of students remained enrolled in the service. The service was found to be acceptable and feasible to students, parents, and school counsellors. Students followed up by the school counsellor reported significant symptom improvements at posttest. Importantly, most of the participants found the service easy to understand (96%, 53/55), easy to use (95%, 52/55), and enjoyable (89%, 49/55). The majority were also comfortable being followed up by the counsellor (82%, 45/55), were likely to use the service again (73%, 40/55) and would tell a friend to use the service (85%, 47/55). However, key questions remain because of the small sample size and lack of a control group. Despite the promise and practicality of the proposed service model, the effectiveness of universal screening, stepped care, and active follow-up from school counsellors for improving young people’s help-seeking and reducing symptoms is still unknown. It is now timely to examine the primary effects of this type of service in comparison with a control group.

**Figure 1 figure1:**
[figure not shown]
Applying Rickwood et al’s help-seeking model to the Smooth Sailing service.

### Objectives

The main objective of this trial is to evaluate the effectiveness of the Smooth Sailing service for improving help-seeking intentions (primary outcome), as well as for improving help-seeking behavior, reducing symptoms of depression, anxiety, distress, and barriers to care, and improving mental health literacy/stigma (secondary outcomes) among secondary school students, in comparison with a school-as-usual control group.

### Hypotheses

The primary hypothesis is that those who receive the Smooth Sailing service will report higher scores of overall help-seeking intentions at 12 weeks posttest compared with baseline. The secondary hypothesis is that compared with students in the control condition, those assigned to intervention will report improved help-seeking behavior and reduced levels of depression, anxiety, distress, and barriers to care, as well as improved mental health literacy and stigma at 12 weeks posttest.

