### Analysis

Data are collected using the Black Dog Institute electronic health platform. Data will be downloaded into Microsoft Excel and exported to SPSS Version 22.0 (SPSS Inc) for analysis. Primary analyses will be undertaken on an intention to treat basis, including all participants randomized, regardless of treatment received. Effectiveness of Smooth Sailing will be established by a change in the GHSQ scores between baseline and 12 weeks using a mixed-effects model repeated-measures analysis. The school will be included in analyses as a random effect to evaluate and accommodate clustering effects. In analyses of scaled secondary variables, methods comparable with those of the primary analysis will be used. An analysis of covariance will be conducted for the secondary outcomes of anxiety, depression, distress, functioning, mental health literacy, and barriers to help-seeking, controlling for baseline scores. To determine the effect of the intervention on help-seeking, 2 binary logistic regression analyses will be used. In model 1, the dependent variable will be help-seeking from adults at 12 weeks. The baseline result will be entered at step 1 in the model, with the study arm entered at step 2. In model 2, the dependent variable will be not seeking help at all at 12 weeks despite a need. The baseline result will be entered at step 1, with the study arm entered at step 2.

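### The primary hypothesis names baseline, not the control arm, as its comparator, and the Analysis section does not name the between-arm contrast that would correct it

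*Protocol article*

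**What the plan says.** The places that bear on the primary contrast, all in the protocol article:

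- **Objectives.** The service is to be evaluated on help-seeking intentions (primary) and the other outcomes "in comparison with a school-as-usual control group". The Objective in the Abstract has the same comparator.
- **Trial Design.** A two-arm, 12-week cluster randomised trial.
- **Hypotheses, primary.** "those who receive the Smooth Sailing service will report higher scores of overall help-seeking intentions at 12 weeks posttest compared with baseline". Baseline is the only comparator named.
- **Hypotheses, next sentence.** "The secondary hypothesis is that compared with students in the control condition, those assigned to intervention will report improved help-seeking behavior". Here the comparator is the control condition.
- **Analysis, population.** "Primary analyses will be undertaken on an intention to treat basis, including all participants randomized, regardless of treatment received".
- **Analysis, primary outcome.** "Effectiveness of Smooth Sailing will be established by a change in the GHSQ scores between baseline and 12 weeks using a mixed-effects model repeated-measures analysis". Then: "The school will be included in analyses as a random effect to evaluate and accommodate clustering effects". No arm or arm-by-time term is named.
- **Analysis, help-seeking behaviour.** For the logistic models the arm is explicit: "The baseline result will be entered at step 1 in the model, with the study arm entered at step 2".

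Table 5 schedules the General Help-Seeking Questionnaire (GHSQ) at baseline and 12 weeks only.

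**The concern.** A primary hypothesis says which comparison decides the trial. This one compares 12 weeks with baseline among students who get the service, so it can be true or false whatever happens in the control schools. A rise in intentions that would have occurred anyway would confirm it. A real benefit against a declining control arm, with intervention scores flat, would fail it.

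The article itself gives reasons why a shared rise is possible. Control students may take part in any mental health education their school arranges (Control). They receive a sheet of help-seeking resources at each of the three assessments (Harms). They also answer the same 13-source questionnaire twice (General Help-Seeking Questionnaire; Table 5).

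The Analysis section is where a reader would look for the correction. It repeats the baseline-to-12-weeks phrasing and identifies no between-arm quantity for the primary outcome.

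**Working it through.** **1. The statements side by side**

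- Abstract Objective, Objectives and Trial Design: intervention against control.
- Secondary hypothesis: intervention against control.
- Primary hypothesis: 12 weeks against baseline, in those receiving the service.
- Analysis, primary outcome: baseline to 12 weeks, all randomised participants, arm contrast not named.

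The third line contradicts the first two. The fourth is compatible with either reading, so it does not resolve the contradiction.

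**2. What the literal hypothesis would allow (illustration)**

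The plan attaches no figure to this contrast, so there is none to reproduce.

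Inputs from Sample Size: 16 schools of about 100 students, 20% attrition, baseline-to-endpoint correlation r = 0.5, intraclass correlation (ICC) 0.02, two-sided alpha 0.05, effect size 0.20.

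Assumptions of this review: 8 schools per arm, the ICC of 0.02 applied to change scores, and a shared drift d in both arms with zero treatment effect.

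- Completers per school: 100 × 0.80 = 80. Intervention arm: 8 × 80 = 640.
- SD of change, in units of the outcome SD: √(2(1 − r)) = √(2 × 0.5) = 1.
- Design effect: 1 + (80 − 1) × 0.02 = 2.58.
- SE of the mean within-arm change: √(2.58/640) = 0.0635.
- Chance of a significant favourable change: P = 1 − Φ(1.96 − d/SE).
- d = 0.10: 1.96 − 0.10/0.0635 = 0.385, so P = 0.35.
- d = 0.20: 1.96 − 0.20/0.0635 = −1.19, so P = 0.88.

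Sensitivity to the clustering assumption, still with 640 completers:

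| Assumption | SE | d = 0.10 | d = 0.20 |
|---|---|---|---|
| No clustering of change (design effect 1) | √(1/640) = 0.0395 | 72% | nearly 100% |
| 80 completers per school (design effect 2.58) | 0.0635 | 35% | 88% |
| 240 completers per school, i.e. 300 less 20% (design effect 1 + 239 × 0.02 = 5.78) | √(5.78/640) = 0.0950 | 18% | 56% |

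In a between-arm test a drift common to both arms cancels, and the chance of a wrong favourable result stays at 2.5% in every row. The larger drift, 0.20 SD, equals the effect size used to size the trial.

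**The case against.** The strongest reply is that the article plainly intends a between-arm comparison. The Abstract, Objectives, Trial Design and Discussion all say so, and the Introduction motivates the trial by the pilot's lack of a control group. Within the Analysis section, intention to treat over everyone randomised makes little sense for a model of the intervention arm alone. The scaled secondary outcomes are to be analysed by methods similar to the primary one, and their hypothesis is between arms. An unnamed arm-by-time term is also the kind of detail that a condensed article leaves to the full protocol or SAP.

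Most of this stands, and it limits the point. A reader might infer that the Analysis section sets a within-arm success criterion and so discards randomisation. The text does not support that: it leaves the arm contrast out but never restricts the model to one arm. A reader might also infer that the primary hypothesis defines a population of those treated. That is weak, because the adjacent hypothesis speaks of assignment and the Analysis section states intention to treat. Regression to the mean is likewise a weak mechanism here, since students are not selected on their scores.

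The reply does not rescue the primary hypothesis itself. Stating the primary comparison is the protocol's task. An SAP that specified an arm-by-time term would be right, but it would conflict with the hypothesis as published.

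The percentages are also open to challenge. The article gives no drift, the ICC is stated only for the design effect at 300 per school, and Results reports ten intervention schools rather than eight. The table rows are examples and not bounds.

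**Conclusion.** The primary hypothesis is wrong as written: its comparator contradicts the objective, the design and the secondary hypothesis. The Analysis section is ambiguous on the same point and does not repair it. Both should be corrected before results are reported, because this wording defines success on the primary outcome.

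The documents do not show that the investigators plan an uncontrolled analysis. The conclusion is that the stated hypothesis permits a favourable reading with no between-arm difference. How often that would happen depends on a drift that nobody has specified. The figures of about 35% and 88% hold only under the stated assumptions, and the textual contradiction does not depend on them.

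**What to change.** 1. **Hypotheses.** Reword the primary hypothesis: students in schools assigned to Smooth Sailing will have higher GHSQ totals at 12 weeks than students in schools assigned to control, adjusted for baseline.
2. **Analysis.** State that effectiveness is judged on that between-arm difference, two-sided at 5%, by intention to treat, with school as a random effect. Name one estimator: the arm effect in a baseline-adjusted model, or the arm-by-time term at 12 weeks. With only two GHSQ occasions, the latter is the between-arm difference in mean change.
3. **Within-arm change.** Label it as descriptive.

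The cost is a few sentences, with no new data and no change to design or conduct. The article reports that data collection has ended and analysis is under way, so the correction should be dated and described as bringing the hypothesis into line with the published objective.

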## Methods

### Trial Design

This clinical trial protocol adheres to the Standard Protocol Items: Recommendations for Interventional Trials 2013 guidelines [31] (see Table 1). This study is a 2-arm 12-week cluster randomized controlled trial (RCT). Data are collected at 3 intervals: baseline, 6 weeks, and 12 weeks posttest with the primary outcome measure assessed at 12 weeks posttest.

### Randomization

Assignment of schools to the control or intervention condition is carried out according to the International Council for Harmonisation guidelines [32] and performed by a researcher not involved in the day-to-day conduct of the trial. Schools are allocated to a single condition (cluster design) to avoid contamination and for administrative convenience [33]. A minimization approach [34,35] is used to ensure balance across conditions in terms of the Index of Community Socio-Educational Advantage level (<1000 vs ≥1000), gender mix (coeducational vs single sex), and year level involved (year 9 students only vs multiple or other years). Minimization is undertaken in StataCorp LLC Stata statistical software version 14.2 using the rct_minim procedure [36]. The pool of already available schools is sorted in random order using the Excel 2003 data analysis random number generator and entered into the minimization routine in ascending order using the factors specified above. Subsequent schools are assigned to an intervention arm using rct_minim in the order that they join the trial and provide complete information. As this trial uses a no-treatment comparator control group, participants and researchers are not blinded to the allocation assignment.

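### Schools are minimised on three factors, but no stated analysis model includes them; where the factors are prognostic, models with a school effect are conservative and lose some power

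*Protocol article*

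**What the plan says.** **Allocation (protocol article, Randomization).** "A minimization approach [34,35] is used to ensure balance across conditions in terms of the Index of Community Socio-Educational Advantage level", split at 1000. The other two factors are "gender mix (coeducational vs single sex), and year level involved (year 9 students only vs multiple or other years"). All three are binary and belong to the school, which is the unit randomised.

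**Primary analysis (Analysis).** "Effectiveness of Smooth Sailing will be established by a change in the GHSQ scores between baseline and 12 weeks using a mixed-effects model repeated-measures analysis". On clustering: "The school will be included in analyses as a random effect to evaluate and accommodate clustering effects". No other term is named.

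**Scaled secondary outcomes (Analysis).** Methods are to be comparable with the primary analysis. The ANCOVAs are described as covering a list of outcomes that ends "and barriers to help-seeking, controlling for baseline scores". Baseline is the only covariate named.

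**Help-seeking behaviour (Analysis).** Both logistic models are written out term by term. For the first: "The baseline result will be entered at step 1 in the model, with the study arm entered at step 2". The second uses the same two terms.

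The Results section reports 22 schools randomised, 10 to intervention and 12 to control.

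**The concern.** Balancing the arms on a prognostic school-level factor removes that factor's contribution from the true sampling error of the arm difference. A model that omits the factor still counts its spread as unexplained variation between schools. The reported standard error is then larger than the true one, the confidence interval is too wide, and the test rejects less often than its nominal level. The analysis does not follow the restricted allocation, and the benefit of the restriction is partly lost.

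This matters more in a trial with few clusters. With about 20 schools, between-school variance is a large part of the error of the arm contrast, so a factor that explains part of it can change power noticeably.

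**Working it through.** **1. Which models name the factors.**

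| Analysis | Terms named in the Analysis section | Minimisation factors |
|---|---|---|
| Primary, GHSQ | school random effect | none |
| ANCOVAs | baseline score (school effect by the general sentence) | none |
| Logistic models 1 and 2 | baseline result, arm | none |

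**2. Inputs.** From Sample Size: effect 0.20 SD, two-sided alpha 0.05, baseline-endpoint correlation 0.5, ICC 0.02, attrition 20%, N = 1600. From Results: 10 and 12 schools. Analysed per school: m = 1600 × 0.8 / 22 = 58.2. Residual variance after baseline adjustment: 1 − 0.5² = 0.75. The share R² of between-school variance explained by the three factors is not in the documents, so it is varied.

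The article gives no power figure for 22 schools to reproduce. Its 1600 does not follow from its own inputs: with ANCOVA and 100 per school, 590 × (1 + 99 × 0.02) / 0.8 = 2198. Nothing below depends on that; 1600 is taken as given.

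**3. Standard error of the arm difference.**

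SE² = (1/10 + 1/12) × [0.02 × 0.75 × (1 − R²) + 0.98 × 0.75 / 58.2]

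- R² = 0: 0.1833 × (0.0150 + 0.0126), SE = 0.0712. Between-school variance is 0.0150 / 0.0276 = 54% of the bracket.
- R² = 0.25: 0.1833 × (0.01125 + 0.0126), SE = 0.0662.
- R² = 0.50: 0.1833 × (0.0075 + 0.0126), SE = 0.0608.

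The unadjusted model reports about 0.0712 throughout.

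**4. Power.** Adjusted: noncentral t with 22 − 5 = 17 df. Unadjusted: the 20-df cut-off times the reported SE, 2.086 × 0.0712 = 0.1485, set against the true SE. For R² = 0.25, (0.20 − 0.1485) / 0.0662 = 0.78, a normal probability of about 78%. For R² = 0.50, 0.0515 / 0.0608 = 0.85, about 80%. The table gives simulated values for the unadjusted test.

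| R² | 22 schools: unadjusted / adjusted | Type I error, unadjusted | 16 schools: unadjusted / adjusted |
|---|---|---|---|
| 0 | 76.3% / 75.4% | 5.0% | 66.7% / 64.9% |
| 0.10 | 76.8% / 77.7% | 4.3% | 67.1% / 67.7% |
| 0.25 | 77.8% / 81.3% | 3.3% | 67.8% / 72.2% |
| 0.50 | 79.7% / 87.3% | 1.9% | 69.4% / 80.5% |

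The unadjusted powers shift by up to about 2 points with how the factor spread is simulated; the pattern does not change. Break-even lies between R² = 0 and about 0.10.

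**5. The primary model.** Write a student's score as a school intercept, plus any stable factor effect, plus the rest. In the difference between 12 weeks and baseline, both the school intercept and the stable factor effect cancel. With a school random intercept only, adding factor main effects therefore leaves the arm-by-time contrast unchanged. A gain requires that schools differ in change and that the factors predict that difference. If so, an unweighted change score has variance 2 × (1 − 0.5) = 1.0. With ICC 0.02 assumed for change, power for 22 schools is 64.8% / 69.4% at R² = 0.25 and 65.9% / 76.6% at R² = 0.50 (unadjusted / adjusted).

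**The case against.** **The article is condensed.** The primary-model sentences do not name arm, time or their interaction, all of which must be present. Silence on covariates there is not exclusion, and a fuller analysis plan may list them. This stands as a limit on the point for the primary model. It is much weaker for the ANCOVAs, where the adjustment variable is named, and weakest for the logistic models, where the terms are enumerated.

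**Stable school differences cancel from change.** This is correct under a school random intercept only (step 5). The primary analysis is affected only if school differences in change are modelled and the factors predict them.

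**Power loss is not certain.** A reader might infer that leaving the factors out necessarily costs power. The documents do not support that: they give no estimate of how strongly the factors predict any outcome, baseline scores may already absorb part of the school variance, and at R² = 0 adjustment is slightly worse.

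**The direction is not the same everywhere.** A reader might infer that all stated standard errors are too large. If the general sentence on the school effect does not reach the logistic models, theirs would tend to be too small. The missing factors remain a mismatch there, but the conservative direction does not carry over.

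**Ten against twelve schools is not imbalance.** These are arm counts. The article does not report the distribution of any factor by arm, so no residual imbalance can be read from them.

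**Conclusion.** The mismatch holds: three factors restrict the allocation and no stated model contains them. It is clear for the ANCOVA and logistic models, and conditional for the primary model.

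The consequence is one of efficiency. Where a school effect is fitted and the factors are prognostic, the test is conservative and intervals are too wide. In the illustration with residual variance 0.75 and 22 schools, adjustment gains about 4 points of power at R² = 0.25 and about 8 at R² = 0.50. With the planned 16 schools the gains are about 4 and 11. If the factors explain nothing, about 1 to 2 points are lost. Reading this as a threat to validity would go too far: type I error falls below 5% rather than above it.

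The figures assume equal school sizes, a cluster-level t-test, ICC 0.02 and perfect balance on the factors. Minimising 16 to 22 schools only approximates that balance.

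**What to change.** Add the three minimisation factors, coded as for allocation, as fixed effects in the ANCOVA and logistic models. In the primary repeated-measures model, enter them with their interaction with time, because main effects alone need not affect the change contrast. Report the models without the factors as a sensitivity analysis. State in the same passage whether the school random effect applies to the logistic models. If the factors are to be left out, give the reason.

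The cost is wording, since the factors were needed to allocate every school, and 3 of 20 between-school degrees of freedom. The Results section says the data are already under analysis, so record when the adjusted model was fixed relative to any comparison of the arms.
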